### Cardiac dysfunction definitions

- **Left ventricular (LV) systolic dysfunction** is the association of a LV fractional area change less than 40% plus an aortic velocity time integral (VTI) less than 14.^(13,28)^- **Right ventricular (RV) failure** is the association of RV dilatation (RV/LV area > 1 plus a CVP at least greater than 8mmHg).^(13,28)^

### Cardiac dysfunction suggested management

- In the case of LV systolic dysfunction, a low dose of dobutamine may be considered, starting with 2.5mcg/kg/minute and up to 7.5mcg/kg/minute. Dobutamine should be stopped if HR increases > 20% over 120 bpm or arrhythmias, ischemia or hypotension develop.^(13,28)^- In the case of RV failure, MV settings should be adjusted to decrease PEEP less than 10cmH2O and limit plateau pressure below 28cmH2O. If patients develop severe ARDS, the prone position should be considered. From a hemodynamic point of view, no further fluid administration is recommended.^(13,28)^

### Additional fluid challenges

In patients with persistent abnormal CRT and for whom cardiac dysfunction is excluded by CCE, further fluid responsiveness assessment is warranted. If patients present fluid responsiveness + status, additional fluid challenges will be administered following the same safety rules as mentioned above.

#### Vasopressor test

In patients with a previous history of chronic hypertension and persistently abnormal CRT after following all previous resuscitation steps, an open-label vasopressor test will be performed, increasing MAP up to 80 - 85mmHg using progressive incremental doses of norepinephrine. Parameters will be reassessed after 1 hour. If CRT improves, norepinephrine will be titrated to maintain this new MAP goal throughout the study period. If goals are not achieved despite increasing MAP or adverse effects are observed (HR > 130 bpm, arrhythmias, or evident cardiac ischemia), the norepinephrine dose will be reduced to the level before the vasopressor test, and the protocol will move to the next step.(4,32,33)

#### Inodilator test

An open-label test of dobutamine at a fixed 5mcg/kg/ minute dose (at the discretion of the attending physician) will be started in nonchronic hypertensive patients with persistent abnormal CRT and negative fluid responsiveness status. Capillary refill time will be controlled after 1 hour, as noted in the vasopressor test. If still abnormal, dobutamine will be discontinued, and no further action will be taken during the study period. Dobutamine will be maintained throughout the study period in those favorably responding to the open label inodilator test. As a safety measure, inodilators will be stopped if HR increases > 20% over 120 bpm or arrhythmias, ischemia or hypotension develop.^(4)^ Patients in whom dobutamine was started earlier due to LV dysfunction should not be subjected to the inodilator test.^(4,32,33)^

### Capillary refill time assessment

Capillary refill time will be measured by applying firm pressure to the ventral surface of the right index finger distal phalanx with a glass microscope slide. The pressure will be increased until the skin is blank and then maintained for 10 seconds. The time for return of the normal skin color will be registered with a chronometer. A CRT > 3 seconds will be considered abnormal.^(4,32,33)^

### Standard care group

Patients allocated to the standard care group will be managed by the clinical staff according to standard practice at their sites, including decisions about hemodynamic and perfusion monitoring and all treatments, but should follow general recommendations of the Surviving Sepsis Campaign to avoid extremes of clinical practice.^(2)^ These recommendations include basic hemodynamic targets, such as a MAP > 65mmHg, HR < 120bpm, oxygen saturation (SatO_2_) > 94%, hemoglobin (Hb) > 7 - 8gr/dL, and the use of norepinephrine as the first vasopressor and crystalloids as the fluid of choice. All data regarding the insertion of invasive monitoring devices, intravenous-fluid resuscitation, vasoactive support, MV, and other supportive therapies will be collected by the study coordinator or monitors. Leading investigators at a site will not serve as the bedside treating physician for patients in the standard care group.

### Safety measures

The protocol can be stopped at any moment for safety considerations during the 6-hour study period if the attending intensivist considers that the patient has developed unexpected and severe complications or conditions that under his judgment require liberalization of management. This action must be reported on the case report form, and the patient will be followed up with major outcomes and included in the intention-to-treat analysis. Specific safety measures for fluid administration, vasopressor and inodilator tests are provided above and in the Manual of Operations.

In addition, even if resuscitation is stopped after achieving the CRT target in the CRT-P group, further hemodynamic interventions may be decided by attendings for interpreting and addressing unstable or severely abnormal circulatory variables, such as HR > 130 bpm, MAP less than 60mmHg with norepinephrine > 0.5mcg/ kg/minute, among others.

### Suspected unexpected serious adverse reaction

Any adverse event that occurs in a clinical trial subject and is assessed by the study investigator as being unexpected, serious and as having a reasonable possibility of a causal relationship with the study procedure will be reported. Reports of these reactions are subject to expedited submission to health authorities. Suspected unexpected serious adverse reactions will be analyzed by the SCC and DSMB.

### Data collection and management

Study follow-up and the variables that will be collected are described in table 1.

**Table 1 t1:** Relevant variables to be registered during the study period

Baseline
Demographics, comorbidities, APACHE-II score, SOFA score
Sepsis source, treatment, adequacy of treatment, time from shock initiation to first antibiotics
Pre-ICU resuscitation administered fluid and fluid balance, AKI-KDIGO criteria^(19,20)^
Hemodynamics: HR, SAP, MAP, DAP, CVP, NE dose
Perfusion variables: lactate, ScvO2, delta pCO2(v-a), hemoglobin, CRT, mottling score
**Evolution**
SOFA score at 8, 24, 48 and 72 hours and at 4, 5 and 7 days
AKI criteria at 8, 24, 48 and 72 hours
Hemodynamics hourly up to 6 hours
Fluid administration and balance at 6, 24, 48 and 72 hours
Complete perfusion assessment at 6, 24, 48 and 72 hours
Register of vasoactive drugs and dobutamine/milrinone use
Register of CCE
Register of FR status and techniques
Register of MV and RRT techniques
Adjuvant therapies: high-volume hemofiltration, use of vasopressin, epinephrine, others
Follow-up until 28 days for use of MV, RRT and vasopressors
All-cause mortality at hospital discharge and at 28 and 90 days
Cause of death

APACHE II - Acute Physiology And Chronic Health Evaluation II; SOFA - Sequential organ failure Assessment; ICU - intensive care unit; AKI - acute kidney injury; KDIGO - Kidney Disease: Improving Global Outcomes; HR - heart rate; SAP - systolic arterial pressure; MAP - mean arterial pressure; DAP - diastolic arterial pressure; CVP - central venous pressure; NE - norepinephrine; ScvO2 - central venous oxygen saturation; delta pCO2(v-a): difference between central venous carbon dioxide pressure and arterial carbon dioxide pressure; CRT - capillary refill time; CCE - critical care echocardiography; FR - fluid responsiveness; MV - mechanical ventilation; RRT - renal replacement therapy.

### Data handling and record keeping

Individual patient data will be handled as ordinary chart records and will be kept according to the legislation (e.g., data protection agencies) of each participating country. Data will be directly registered in the electronic case report form which is Health Insurance Portability and Accountability Act (HIPAA) compliant. Data will be captured and stored at Erasmus Medical Center for further quality control and statistical analysis.

All original records (including consent forms, case report forms, serious adverse event reports, and relevant correspondence) will be retained at trial sites to allow inspection by relevant authorities. The trial database will be maintained for and anonymized if requested for revision.

### Quality control

Several procedures will assure data quality, including online study protocol and electronic form registry training and availability from the SCC to resolve issues or problems that may arise. A data quality team (DQT) will ensure the adequacy of the online registry, identify missing values and inconsistencies, and contact study centers and SSC to promptly solve these issues.

### Missing data management

Missing data will be reported in the publication. If further analyses reveal substantial missingness, multiple imputation will be considered.

### Sample size

We assumed a mortality of 39% in the control group, which is based on the mortality of the whole cohort in ANDROMEDA-SHOCK.^(4)^ Given that the intervention arm includes several new steps aimed at better tailoring fluid administration, we expect a further decrease in the use of fluids. Based on ANDROMEDA-SHOCK’s data, this new algorithm based on pulse pressure, diastolic blood pressure, and echocardiography could reduce fluid administration in at least 60% of these patients. Previous studies have shown that a reduction in fluid administration is associated with better outcomes. Thus, we estimate a 6% reduction in mortality. Estimates of the number of days needing life support truncated at 28 days and length of hospital stay in the control group were based on data from the ANDROMEDA-SHOCK control group.

For the control group, we assumed a 28-day mortality of 39%, a number of days needing life support truncated in 28 days of 5.6 (standard deviation - SD, 6.7) and a length-of-hospital stay truncated in 28 days of 15.6 days (SD, 10.1). We considered that the experimental group treatment would reduce mortality to 33% (absolute reduction of 6%), shorten days using life support to 4.3 (SD, 6.2) and shorten length of hospital stay to 14 days (SD, 9.9). Length-of-hospital and number of days needing life support were simulated assuming a beta-binomial distribution within 28 days using parameters acquired in the ANDROMEDA-SHOCK trial.^(4)^

With 1,500 patients enrolled, the trial will have a power of 88% to show superiority in the win-ratio outcome for a two-sided α of 0.05.

### Statistical analysis

A detailed statistical analysis plan will be elaborated and published before the trial database is locked and data are analyzed. The fundamental characteristics of the statistical analysis plan are described below.

All patients will be analyzed in the groups they were assigned to independently of adherence to trial protocol, i.e., analysis will follow the intention-to-treat principle. For patients with missing data for the primary outcome, we will impute missing primary outcome data using multiple imputation chains. Variables to be used for imputation will be specified in the statistical analysis plan and will likely include age, enrolling site, and Acute Physiology and Chronic Health Evaluation (APACHE) II score. The medians of the imputed results (or the most frequent category) will be used for the analysis. Categorical variables will be presented as numbers and percentages. Continuous variables will be presented as the mean and SD or median and interquartile range if the distribution is asymmetrical.

We will assess the effect of the trial treatment compared to the control group treatment on the hierarchical primary outcome using the win ratio method proposed by Dong et al.,^(34)^ which is based on the Pocock et al. win ratio,^(35)^ using treatment as a fixed effect. All patients in the treatment group will be compared to all patients in the control group, one pair at a time, following the hierarchical primary outcome: all-cause mortality within 28 days, time to cessation of vital support within 28 days, and length of hospital stay (truncated at Day 28).

Thus, in each pair, mortality will be compared. If only one of the patients died, a win will be counted for the group of surviving patients. If both patients in the pair died, this will be considered a tie (and no further comparisons will be made for this pair). If both patients survive past 28 days, then the time to cessation of vital support will be compared. A win will be counted for the treatment group, which has the patient with the shortest time to cessation of vital support. If the number of days up to cessation of vital support is the same within the pair, then the third outcome in the hierarchy, namely, length of hospital stay, will be compared. A win will be counted for the treatment group that has the patient with the shortest length of hospital stay. Of the length of stay (in number of days) is identical, then this will be counted as a tie.

The win ratio is calculated as the total number of wins in the experimental group divided by the total number of wins in the control group. A value greater than 1 indicates better outcomes in the experimental group. The bootstrap resampling method will be used to calculate the 95% confidence interval (95%CI) for the win ratio and P value for the hypothesis test.

We will assess the treatment effect on the primary hierarchical composite outcome according to the following subgroups: age (< or ≥ 65 years); APACHE II (< or ≥ 25 points); SOFA (< or ≥ 10 points); baseline lactate (< or ≥ 4mmol/L); baseline CRT (< or ≥ 3 seconds); septic shock source (lung *versus* abdominal *versus* urinary *versus* soft tissues *versus* bacteremia *versus* other); and MV at inclusion.

P values will be reported for the primary outcome analysis, and p values for interaction will be reported for the subgroup analyses; the remaining outcomes will be reported with the mean effect and 95%CI. Given the potential for type I error due to multiple comparisons, the findings for the analyses of the secondary and tertiary outcomes should be interpreted as exploratory. All tests are 2-sided with an α level of 0.05. All analyses will be performed with the latest version of R software (R Foundation for Statistical Computing).

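### Collapsing the multiple imputations of the primary outcome to a median or most frequent category makes them a single deterministic fill that understates uncertainty and scores too many missing patients as alive

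*Protocol article*

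**What the plan says.** The Statistical analysis section of the protocol article defers the details to a later statistical analysis plan (SAP) but sets out what it regards as the fundamentals. On missing data it commits to a method: "For patients with missing data for the primary outcome, we will impute missing primary outcome data using multiple imputation chains". The predictors are left to the SAP, with an indication that they "will likely include age, enrolling site, and Acute Physiology and Chronic Health Evaluation (APACHE) II score". What is done with the imputations is not deferred: "The medians of the imputed results (or the most frequent category) will be used for the analysis".

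The same section defines the win ratio with 28-day death as the first level of the hierarchy, and obtains the confidence interval and P value by bootstrap. It does not say that imputation is repeated within the bootstrap.

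A separate, general section, Missing data management, says: "If further analyses reveal substantial missingness, multiple imputation will be considered".

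**The concern.** Multiple imputation gives valid inference because each completed dataset is analysed and the results are pooled, so that disagreement between imputations enters the standard error. Reducing the imputations to one value per patient before the analysis removes that component. The bootstrap then treats the filled values as if they had been observed.

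The second problem has a direction. Death is less likely than survival for most patients at the planned event rates. The most frequent imputed category is therefore alive unless a patient's predicted risk is near or above 50%. Deaths are under-scored at the level of the hierarchy that overrides all others, and the arm with more missing outcomes gains. This happens even when data are missing at random and the imputation model is correct. The rule governs the trial's only confirmatory test.

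**Working it through.** **Inputs from the Sample size section.** Control arm: 28-day mortality 39%, life-support days 5.6 (SD 6.7), hospital stay 15.6 days (SD 10.1). Experimental arm: 33%, 4.3 (SD 6.2) and 14 (SD 9.9). Day counts are beta-binomial on 28 days; 1,500 patients are allocated 1:1, so 750 per arm; two-sided alpha is 0.05.

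**Assumptions, because the article gives no figure.** Missing fraction 0-10% per arm; number of imputations M from 5 to 100; discrimination of the imputation model (AUC) 0.50 to 0.79.

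**The plan's own figure.** The article gives no number for the effect of missing data. Its 88% power was not reproduced: simulation from the stated inputs gives about 98.9%, and 93.6% to 99.9% over variants with the full stated effects. The joint distribution of the components is not stated, and the mismatch does not bear on this point. The null calculation in step 2 uses only the control inputs.

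**Step 1: how many missing patients are scored dead.** If every patient has risk p, the most frequent category is dead with probability P(X > M/2) + ½P(X = M/2), where X is binomial(M, p).

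| | M=5 | M=10 | M=20 | M=50 | M=100 |
|---|---|---|---|---|---|
| p = 36% | 25% | 19% | 10% | 2% | 0.2% |
| p = 39% | 30% | 25% | 16% | 6% | 1.3% |

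With risks that vary between patients (logit-normal, mean 36%) and M = 5/20/100, the shares scored dead are:
- AUC 0.61: 26/16/9%
- AUC 0.68: 28/22/19%
- AUC 0.74: 30/26/25%
- AUC 0.79: 31/29/28%

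At 36% mortality, between 0.2% and 31% are scored dead, so 69% to 99.8% are scored alive. The expected share alive is 61-67%. Deaths are under-scored in every setting tried.

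**Step 2: effect on the null win ratio.** Fit each beta-binomial by moments: π = mean/28; ρ = (SD²/[28π(1−π)] − 1)/27; a = π(1/ρ − 1); b = (1−π)(1/ρ − 1).
- Support: π = 0.200; 44.89/4.48 = 10.02; ρ = 0.334; a = 0.399, b = 1.595; median 3 days.
- Stay: π = 0.557; 102.01/6.909 = 14.77; ρ = 0.510; a = 0.536, b = 0.426; median 17 days.

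Give both arms the control distribution, with support and stay independent among survivors. Replace a fraction m of each arm by fills: a share d dead, the rest alive with 3 support days and 17 hospital days. Let W and L be the probabilities that a random pair is won or lost by the arm with more missing data. The standard error (SE) of log(W/L) is the asymptotic U-statistic value with 750 per arm.

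For 6% against 2% missing and d = 0: W = 0.4357, L = 0.4207, win ratio 1.036, SE 0.0678. Then z = ln(1.0357)/0.0678 = 0.52, and rejection = Φ(−1.96 + 0.52) + Φ(−1.96 − 0.52) = 8.1%. The mechanism shows in the apparent mortality: 0.94 × 39% = 36.66% against 0.98 × 39% = 38.22%, with no true difference.

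| Missing | d = 0 | d = 10% | d = 20% | d = 28% |
|---|---|---|---|---|
| 6% v 2%: win ratio | 1.036 | 1.026 | 1.017 | 1.009 |
| 6% v 2%: type I error | 8.1% | 6.7% | 5.7% | 5.2% |
| 3% v 0%: type I error | 6.7% | 6.0% | 5.4% | 5.1% |

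With all fills alive, 2% v 1% and 3% v 2% each give 5.2%. Equal missingness gives a null win ratio of exactly 1.

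**Step 3: collapse against pooling, by simulation** (M = 20, 700 replicates, imputation from the true model).
- SE under the planned effect: collapsed 0.0673 against pooled 0.0693 at 5% missing per arm, 1 − 0.0673/0.0693 = 2.9% smaller. At 10% it is 0.0670 against 0.0709, 5.5% smaller. The complete-data SE at 10% is 0.0676, so collapsing appears more precise than having all the data.
- Null, 2% missing in the experimental arm against 8% in control: collapsed win ratio 0.968 with 7.7-8.4% rejection (AUC 0.50), or 0.984 with about 4.7% (AUC 0.68). Pooled: 0.999 to 1.001.
- Planned effect, 10% missing per arm: the complete-data win ratio of 1.338 becomes 1.308 when collapsed with arm left out of the imputation, and 1.387 with arm included (coverage 0.907). Pooled by arm: 1.338.
- Null with equal missingness of 1-10%: collapsed rejection about 4-6%. The Monte Carlo error near 5% is √(0.05 × 0.95/700) = 0.8 points, so this shows no clear inflation.

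**The case against.** **The numbers depend on assumptions.** No missing fraction is given, and nothing in the article points to a four-point imbalance. Outcomes run to 28 days, patients whose protocol is stopped are still followed, and a data quality team pursues missing values. This stands. It limits the size of the effect but does not make the rule sound.

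**A reader might infer that almost every missing patient is scored alive.** That requires weak predictors and about 50 or more imputations. The article states neither, and it names predictors under which some high-risk patients would be scored dead. Only the range in step 1 is supported.

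**A reader might infer a large loss of the target effect.** Missing 5% in control alone lowers its apparent mortality to 0.95 × 39% = 37.05%, a shift of 1.95 points. That supposes no loss in the other arm. With 5% missing in both, the contrast is 37.05% − 31.35% = 5.70 points instead of 6.

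**A reader might infer that treatment arm is wrongly left out of the imputation model.** The list of variables is provisional and expressly left to the SAP, so its absence is not an error.

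**A reader might infer that the two missing-data statements contradict each other.** Missing data management is general; the rule under Statistical analysis is specific to the primary outcome. The two can be read together, and only a clarification is needed.

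**The sentence could mean the median of the estimates across imputations.** The reference to the most frequent category makes that reading weak, since an estimated win ratio has no category.

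**Pooling was somewhat conservative in the simulations.** With equal missingness it rejected 1.7% to 4.9% under the null. Those simulations imputed from the true model, which favours both methods. They do not establish how far collapsed intervals would under-cover in practice.

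**Conclusion.** The point holds as a flaw in a stated rule. The median or most-frequent-category step is single deterministic imputation: it discards between-imputation variance and under-scores death at the top of the hierarchy, to the advantage of the arm with more missing outcomes.

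The size is modest and conditional. The 8.1% type I error is a worst case that needs unequal loss and every fill alive; a well-predicting model brings the same imbalance down to about 5.2%. Bias in the estimate under a true effect does not need imbalance, as the 10%-per-arm result in step 3 shows. All these figures rest on assumed missingness, M and AUC, and on independence of the lower tiers. The rule should be fixed before analysis, but the documents do not show that it invalidates the trial.

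**What to change.** Delete the median/most-frequent-category sentence. Replace it with one of two procedures:
1. Compute the win ratio and its bootstrap variance in each imputed dataset, and pool log(win ratio) by Rubin's rules.
2. Repeat the imputation within each bootstrap sample, with no median or mode step.

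When the SAP fixes the imputation variables, include treatment arm. Adding arm while keeping the collapse would not repair the problem, as the 1.387 in step 3 shows.

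As a clarification, state under Missing data management that its conditional wording does not apply to the primary outcome.

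The cost is a wording change in the protocol or SAP, a little programming and slightly wider intervals. No change to sample size or data collection is needed.

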### Randomization and blinding

A randomization sequence with a 1:1 allocation will be generated using a computer program and captured using an electronic data management system. Study group assignment will be performed by means of randomized permuted blocks of variable size. Allocation concealment will be maintained by means of central randomization.

Given that the intervention will be administered to critically ill patients (mostly sedated), blinding of these patients is not necessary. Because this is a nonpharmacological intervention, blinding the medical team is not feasible.

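### The primary win ratio ignores baseline severity although APACHE II is collected; stratifying on it would be more efficient, with a gain that depends on how prognostic the score is

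*Protocol article*

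**What the plan says.** Under Statistical analysis, the protocol article forms the win ratio from every possible treated-control pair: "All patients in the treatment group will be compared to all patients in the control group, one pair at a time". Pairs are judged on 28-day death, then time to cessation of vital support, then hospital stay. For two deaths the rule is "If both patients in the pair died, this will be considered a tie". The estimate is total experimental wins over total control wins, with a bootstrap interval and p value. Treatment is the only effect named, and no strata or covariates are mentioned.

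Randomisation does not balance severity by design either. Under Randomization and blinding, "A randomization sequence with a 1:1 allocation will be generated using a computer program", in permuted blocks of variable size, and no stratification factor is given.

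Severity is nevertheless measured. The baseline part of Table 1 lists "Demographics, comorbidities, APACHE-II score, SOFA score". APACHE II also defines a subgroup (cut at 25 points) and is named as a likely imputation variable.

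Under Sample size: "With 1,500 patients enrolled, the trial will have a power of 88% to show superiority in the win-ratio outcome". The two-sided α is 0.05.

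**The concern.** When all patients are compared with all others, many pairs set a mildly ill patient against a very sick one. Severity then largely decides who wins, whichever arm each patient is in. Such pairs add noise to the treatment comparison.

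Two things are at stake. The first is power: a baseline score that predicts the outcome can remove part of this noise, and the plan does not use it in the one analysis that carries the conclusion. The second is credibility: if the arms happen to differ in severity, the headline result moves with that difference, and in an open-label trial readers will ask about it.

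**Working it through.** **Inputs from the article.** 1,500 patients, 1:1, so 750 per arm; two-sided α 0.05; mortality 39% v 33%; life-support days 5.6 (SD 6.7) v 4.3 (SD 6.2); hospital stay 15.6 (SD 10.1) v 14 (SD 9.9); beta-binomial day counts on 0-28.

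**Inputs assumed.** The article gives no figure for the prognostic strength of APACHE II. A latent severity score stood in for it, with AUC for death from 0.59 to 0.76 and latent correlations of 0-0.5 with support days and 0-0.3 with stay.

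**How pairs split under the planning mortality.**
- Exactly one death: 0.39 × 0.67 + 0.61 × 0.33 = 0.261 + 0.201 = 0.463
- Both dead (tie): 0.39 × 0.33 = 0.129
- Both alive: 0.61 × 0.67 = 0.409

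About 46% of pairs are settled by death alone.

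**The plan's own 88%.** Mortality alone: z = 0.06 / √[(0.39 × 0.61 + 0.33 × 0.67)/750] = 0.06/0.0247 = 2.43, and Φ(2.43 − 1.96) is about 68%. With all three components, and the day counts read as distributions in survivors, simulated all-pairs power was about 98-99% (win ratio about 1.32-1.34). So 88% was not reproduced from the printed inputs. Keeping the full mortality effect and half the effect on support and stay gave 87.9% (win ratio 1.23). That setting was used to examine the gain near the stated power.

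**Stratified statistic.** Pairs are formed only within stratum s, and WR = Σ(W_s/N_s) / Σ(L_s/N_s), where W_s and L_s are experimental wins and losses and N_s is stratum size. The test was a Wald test on log WR with U-statistic variance, the large-sample counterpart of the bootstrap, over 2,000-4,000 trials per scenario.

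**Results with four strata, full mortality effect and half the other effects.** To start from the stated 88% (mean z = 1.96 + 1.175 = 3.135), power = Φ(3.135 × z_strat/z_all − 1.96).

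| Assumed AUC | Correlation with support / stay | Mean z, all pairs | Mean z, 4 strata | Rescaled from 88% | Simulated power, all pairs → 4 strata |
|---|---|---|---|---|---|
| 0.591 | 0.1 / 0 | 3.05 | 3.08 | 88.5% | 85.2% → 86.9% |
| 0.637 | 0 / 0 | 3.09 | 3.14 | 88.8% | 86.7% → 87.6% |
| 0.638 | 0.3 / 0.2 | 3.02 | 3.15 | 90.6% | 86.0% → 89.0% |
| 0.686 | 0.2 / 0.1 | 3.00 | 3.13 | 90.5% | 85.3% → 88.2% |
| 0.684 | 0.4 / 0.3 | 2.97 | 3.22 | 92.5% | 84.8% → 90.5% |
| 0.731 | 0.3 / 0.2 | 2.97 | 3.23 | 92.6% | 84.7% → 90.2% |
| 0.757 | 0.5 / 0.3 | 2.90 | 3.33 | 94.9% | 82.7% → 91.1% |

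Worked row, AUC 0.731: 3.135 × 3.23/2.97 = 3.41; 3.41 − 1.96 = 1.45; Φ(1.45) = 92.6%. The squared ratio (3.23/2.97)² = 1.18 is the equivalent of 18% more patients.

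Gains are larger in points when the starting power is lower, because the power curve is steeper there. Single runs starting from 80-85% therefore exceed the rounded ranges by up to about one point. A median split already captures much of the gain: at AUC 0.731, 91.6% against 92.6% with four strata.

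**At the full printed effects.** All-pairs power is about 98-99% and stratified power 98.7-99.8%, a gain of about 0-1.5 points.

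**Type I error.** Null rejection was 5.4% for all pairs and 5.5-5.8% stratified (2,000 trials; simulation SE √(0.05 × 0.95/2000) = 0.5 points). Nothing here suggests a loss of control.

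**Chance imbalance.** The standardised difference in severity between arms has SE √(2/750) = 0.052, so it exceeds 0.1 SD in about 5% of trials. In a separate simulation (3,000 trials per scenario), among null trials with such an imbalance the all-pairs test rejected 10-16% of the time and the quartile-stratified test 5-7%.

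**The case against.** The strongest reply is that nothing here is an error. An all-pairs win ratio in a 1:1 randomised trial is valid, its type I error is correct, and chance imbalance is part of the sampling error that the interval covers. That stands. A reader might infer that the planned analysis is biased or invalid; the simulations show the opposite. The conditional rejection rates above describe the few trials that turn out imbalanced, not the test overall.

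The second reply concerns size. A reader might infer a fixed benefit of 3-8 points. The documents do not support that: they give no AUC for APACHE II, and at 0.59-0.64 the gain can be as small as 0.5 points. Nor does the article plan for reduced effects on support and stay. At its printed effects there is almost no room for improvement.

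The third is that the change is not free. The estimand becomes a within-stratum win ratio, which lies further from 1 (for example 1.35 against 1.32), and missing scores need handling. Table 1 lists APACHE II under baseline without giving its data window, so it must be confirmed that the score uses only data from before randomisation.

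Finally, the article announces a detailed analysis plan that is not shown and cites a win ratio method that was not at hand. Either might bring in strata. The published text, though, presents the all-against-all comparison as a fundamental feature of the plan, so adding strata would be a change to what is stated.

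**Conclusion.** The point holds as an efficiency improvement worth making, not as the correction of a faulty test. Stratifying on a prognostic score raised power in every scenario examined, without visible cost to type I error. If unstratified power is about 80-88%, the gain is roughly 0.5-4 points for an assumed AUC for death of 0.59-0.64, about 2-5 points for 0.68-0.74 and about 5-8 points for 0.76 or more. If the printed planning effects are realised in full, it is about 0-1.5 points. Protection against chance severity imbalance does not depend on the starting power, but it does require the score to be prognostic.

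The failure to reproduce 88% does not show that figure to be wrong. The article does not say whether the day counts refer to survivors or to all patients, or how the components were correlated.

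**What to change.** Before database lock, and without sight of outcomes by arm, specify a stratified win ratio as the primary analysis:

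- Form pairs only within fixed APACHE II strata, for example tertiles or quartiles.
- Combine wins and losses over strata with weights 1/stratum size.
- Carry out the bootstrap within the same scheme.
- Use a score built from pre-randomisation data and state its data window.
- State a simple rule for a missing APACHE II.
- Keep the all-pairs win ratio as a sensitivity analysis.

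The cost is analysis-plan wording and minor code. No extra patients or data items are needed. The report should say plainly that the primary estimate is a within-stratum win ratio. If the unseen analysis plan already stratifies by severity, it is enough to bring the two texts into line.
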